### Secondary endpoints

Secondary endpoints will include: the number of nodes removed along the right and left RLN; the incidence of pneumonia, defined according to the Revised Uniform Pneumonia Score which includes temperature, leukocyte count, and pulmonary radiography (Table 2) [25]; the incidence of other postoperative complications (e.g., anastomotic leakage, chylothorax), defined according to the Esophagectomy Complications Consensus Group system; the total percentage of surgery-related major postoperative complications (i.e., grade IIIa or higher according to the Clavien–Dindo criteria) [26]; in-hospital, 30-day, and 90-day mortality rates, defined as any death occurring during the same hospitalization and within 30 or 90 days after surgery, respectively; R0 resection rates, defined as microscopically negative proximal/distal and circumferential margins; surgery-related parameters (including thoracic, abdominal, and total surgical time (expressed in minutes); unexpected events and complications occurring during surgery (e.g., massive hemorrhage, perforation of other organs); blood loss during surgery (expressed in milliliters per phase); and number of patients requiring conversion to thoracotomy and related reasons); postoperative recovery parameters (including length of mechanical ventilator use after surgery (expressed in minutes), length of ICU stay (expressed in hours), length of hospital stay (expressed in days), and need for reintubation or readmission to the ICU); quality of life and psychometric measures (including the EORTC QLQ-C30, OES-18, and Hospital Anxiety and Depression Scale (HADS) questionnaires, administered at the following time points: 5 days before surgery; 4 weeks, 3 months, and 6 months after surgery; and on a yearly basis up to 5 years thereafter); and oncological outcomes (including 2-year, 3-year, and 5-year disease-free and overall survival rates).

**Table 2 Tab2:** Revised Uniform Pneumonia Score

Diagnostic criterion	Revised Uniform Pneumonia Score	
	Range	Score
Temperature (°C)	≥ 36.1 and ≤ 38.4	0
	≤ 36.0 and ≥ 38.5	1
Leukocyte count (× 10^9^/L)	≥ 4.0 and ≤ 11.0	0
	< 4.0 or > 11.0	1
Pulmonary radiography	No infiltrate	0
	Diffused (or patchy) infiltrate	1
	Well-circumscribed infiltrate	2

A sum score of 2 points or higher, in which at least 1 point is assigned because of infiltrative findings on pulmonary radiography, indicates the presence of pneumonia

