### Sample size calculation

Based on a preliminary study conducted by our group, the projected rates of successful left RLN LND (according to the definition proposed in the current trial) are 70–75% and 85–90% for VATE and RE, respectively [20]. The purpose of our study is to demonstrate that the rate of successful left RLN LND will be at least 15% higher for RE compared with VATE (based on a conservative 75% rate for VATE). Because our null hypothesis is that the difference between the two arms is ≤15%, we will adopt one-sided testing. In a one-sided test, the “extreme” portion of distribution is decided beforehand as meaning “sufficiently large” (i.e., 15% in our case) [20]. Assuming an alpha error of 0.05 and an 80% power using one-sided two-sample comparisons of proportions under a balanced trial design, a total of 95 patients per treatment arm will be required. Assuming a dropout rate of 10% in the entire study cohort, we plan to enroll a total of 212 patients (i.e., 106 in each arm).

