### Statistical analysis

A formal statistical analysis plan will be prepared by both an independent statistician and the principle investigator ahead of the final data collection (both blinded to treatment allocation and the study results). The final study findings will be released by the study statistician. Data analysis will be performed in patients who will receive RLN LND according to the procedure assigned at randomization and who will have complete follow-up data on nerve palsy recovery status at the 6-month assessment (for confirmation of permanent nerve palsy). A small percentage of patients (estimated 5% maximum) are expected not to undergo the procedure assigned at randomization either because of self-withdraw from the study or because of occurrence of unexpected intraoperative findings (as described in the “Surgical approach” section). Another 5% of patients may potentially be lost to follow-up, resulting in a maximum expected total dropout rate of 10%. We will perform both an in-depth analysis of the reasons for dropout and a comparison of dropouts and completers. The primary outcome will be analyzed using a two-sample proportion test (single-sided). Categorical secondary outcomes will be expressed as frequencies and compared with the Fisher’s exact test. Continuous secondary outcomes will be given as means ± standard deviations (for normally distributed variables) or medians and interquartile ranges (for skewed parameters). Comparisons will be performed using Student’s *t* test and the nonparametric Mann–Whitney *U* test, respectively. The Cochran–Mantel–Haenszel test will be used to examine the differences in categorical outcomes between the two treatment groups after adjusting for study center and use of nCRT. All calculations will be conducted with SAS (version 9.3; SAS Institute Inc., Cary, NC, USA) and SPSS (version 20.0; SPSS Inc., Chicago, IL, USA) statistical packages. *P* < 0.05 will be considered statistically significant.

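### Quality-of-life and HADS scores are assigned two-sample tests that make no stated use of the baseline score or of hospital, which is valid but loses precision

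*Protocol article*

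**What the plan says.** The Secondary endpoints section lists "quality of life and psychometric measures (including the EORTC QLQ-C30, OES-18, and Hospital Anxiety and Depression Scale (HADS) questionnaires" among the secondary endpoints, "administered at the following time points: 5 days before surgery; 4 weeks, 3 months, and 6 months after surgery", and then yearly up to 5 years. A pre-surgery score is therefore planned for every patient.

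The Statistical analysis section sets one rule for all continuous secondary outcomes. On description it says: "Continuous secondary outcomes will be given as means ± standard deviations (for normally distributed variables) or medians and interquartile ranges (for skewed parameters". On testing it says: "Comparisons will be performed using Student’s *t* test and the nonparametric Mann–Whitney *U* test, respectively". No separate rule is given for the questionnaires.

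The only covariate adjustment in that section is the Cochran–Mantel–Haenszel test, used to "examine the differences in categorical outcomes between the two treatment groups after adjusting for study center and use of nCRT". It covers categorical outcomes only. Under Randomization, allocation is stratified by enrolling hospital. The Statistical analysis section also announces a later document: "A formal statistical analysis plan will be prepared by both an independent statistician and the principle investigator". That document is not available here.

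**The concern.** A patient's score before surgery is usually among the best predictors of the same score afterwards. A t or Mann–Whitney test of follow-up scores does not use it. The comparison then has a wider interval than the data allow, and part of any chance difference between arms at baseline stays in the estimate. Hospital is left out in the same way, although randomization is stratified by it and the categorical outcomes are adjusted for center.

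What is at stake is the precision of a named secondary objective. The Background motivates the trial partly by the harm that nerve injury does to quality of life. The sample size was set for the primary endpoint alone, so precision on these scales has to come from the analysis.

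**Working it through.** **The plan's own figure.** The article gives no sample size or power for the questionnaires. The only figure to borrow is the 95 evaluable patients per arm from the Sample size calculation, which was derived for the primary endpoint: "Assuming an alpha error of 0.05 and an 80% power using one-sided two-sample comparisons of proportions under a balanced trial design". The projected success rates there "are 70–75% and 85–90% for VATE and RE, respectively". The pooled one-sided formula without continuity correction returns 95 for 70% against 85%:

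- n = [1.645·√(2 × 0.775 × 0.225) + 0.842·√(0.70 × 0.30 + 0.85 × 0.15)]² / 0.15² = 94.8, rounded up to 95.
- The 75% against 90% that the text says it used gives 79.
- The dropout step agrees: 95/0.9 = 105.6, rounded up to 106.

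The mismatch between 75% and 95 per arm is a separate matter. Here 95 serves only as a working number of patients per arm.

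**Assumptions not in the documents.**

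- r, the correlation between baseline and follow-up score: range 0.3 to 0.6.
- Scores in units of one standard deviation, with the same SD at baseline and follow-up.
- Two-sided 5% tests.
- For power, a true difference of 0.4 SD.

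**Formulas, for one visit.**

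- Variance relative to a t test on follow-up scores: ANCOVA 1 − r²; change-score t test 2(1 − r).
- Unadjusted sample size with the same precision as ANCOVA: 95/(1 − r²) per arm.
- Standard error of the unadjusted difference: √(2/95) = 0.145 SD.
- Difference detectable with 80% power: (1.96 + 0.842) × 0.145 × √(1 − r²). Without adjustment it is 0.41 SD.
- Power: Φ(0.4/(0.145·√(1 − r²)) − 1.96). Without adjustment it is 78.7%.
- Chance baseline difference between arms: SD 0.145, 95% range ±1.96 × 0.145 = ±0.28 SD. An unadjusted follow-up comparison carries r times this.

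| | r = 0.3 | r = 0.5 | r = 0.6 |
|---|---|---|---|
| ANCOVA variance, t test = 1 | 0.91 | 0.75 | 0.64 |
| Variance reduction | 9% | 25% | 36% |
| Equivalent unadjusted n per arm | 104 | 127 | 148 |
| Detectable difference (SD) | 0.39 | 0.35 | 0.33 |
| Power at 0.4 SD | 82.4% | 88.9% | 93.1% |
| Carried-over imbalance, 95% range (SD) | ±0.09 | ±0.14 | ±0.17 |
| Change-score variance, t test = 1 | 1.4 | 1.0 | 0.8 |

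**Change scores.** 2(1 − r) − (1 − r²) = (1 − r)², which is never negative. A change-score t test is therefore never more efficient than ANCOVA, and below r = 0.5 it is worse than ignoring the baseline.

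**Not quantified.** The factor 1 − r² compares ANCOVA with a t test. It does not measure the gain over a Mann–Whitney test on skewed scores. The gain from including hospital cannot be sized either, because the documents give no between-hospital difference.

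**The case against.** The strongest reply is that the rule is generic. It covers operating time, blood loss, length of stay and node counts, most of which have no baseline, and the Statistical analysis section never names the questionnaires. Covariates and repeated-measures models are the kind of detail a condensed article leaves to its analysis plan. This stands in part: the unseen plan may well adjust. But the article is not silent. It names the tests for all continuous secondary outcomes, and an analysis plan that adjusts for baseline would have to replace them.

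Several stronger readings are tempting, and the documents do not support them:

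- **That the tests are invalid or biased.** They are not. Over randomization the unadjusted comparison is unbiased, with no cost in type I error, and its standard error already allows for chance imbalance.
- **That a baseline imbalance carries through in full.** Only r times it does.
- **That raw scores will be tested visit by visit, dropping patients who miss a visit.** The article says neither. A t test on change from baseline would fit the wording and would use the baseline, though less efficiently than ANCOVA. No missing-data rule for the questionnaires is stated.
- **That the questionnaire 5 days before surgery contradicts the visit 2 weeks before surgery in the Follow-up schedule.** One is a questionnaire time and the other a visit time, and both can hold.

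It is also fair to object that the baseline may not be a clean covariate. The Follow-up schedule starts each patient's study at randomization, and the documents do not say whether the questionnaire comes before or after it. In an open-label trial, a score given once the allocation is known could be influenced by it. This objection stands and shapes the fix.

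**Conclusion.** The point holds as a matter of efficiency. For scales with a planned baseline, the article names tests without covariates and states no use of the baseline score or hospital. With r assumed between 0.3 and 0.6, the variance forgone at a given visit is about 9% to 36%, equivalent to having 104 to 148 patients per arm instead of 95. At the low end the gain is modest: power for an assumed 0.4 SD difference moves only from 78.7% to 82.4%. These figures rest on the assumed r, on 95 patients per arm still contributing at the visit, and on the t-test branch of the rule. The point concerns one group of secondary endpoints and leaves the primary comparison untouched. It is worth correcting because the gain costs so little.

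**What to change.** For QLQ-C30, OES-18 and HADS scores, replace the t/Mann–Whitney rule with wording such as:

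> Arms will be compared by ANCOVA at each post-operative visit, or by a mixed model for repeated measures with treatment, visit and their interaction, with the baseline score of the same scale and hospital as covariates.

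The existing rule can stay for continuous outcomes without a baseline. If the analysis plan already specifies such a model, it should say that it supersedes the article's rule for these scales.

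The cost is small: slightly more analysis work and a model assumption for skewed scores, whose residuals should be checked. A mixed model uses patients with some missed visits, but it does not by itself deal with deaths over 5 years, so the handling of scores after death needs its own statement.

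Baseline timing is a minor procedural change, not wording alone. Where possible, the baseline questionnaire should be completed before the allocation is disclosed. Enrolment began in November 2018, so this can apply only to patients not yet randomized. For the others, record whether the questionnaire preceded disclosure and report the unadjusted comparison alongside.

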### Randomization

A computerized randomization tool will be used to randomly allocate patients to either RE or VATE (1:1 ratio). In order to minimize the potential confounding effect of local treatment variables (e.g., postoperative care), patients will be stratified in a 1:1 fashion according to the enrolling hospital. A permuted-block randomization with varying block size will be implemented. Allocation and block size will be concealed from all investigators. Blinding of surgeons is unfeasible because of the obvious technical differences between RE and VATE. However, the occurrence of the study endpoints will be determined from medical records by an independent assessor who will be blinded to the surgical technique used for each case. Patients will have the option to withdraw from the study at any time.

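### Continuous secondary outcomes have only unadjusted tests although randomization is stratified by hospital; if center is prognostic, the t test is conservative and can lose power

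*Protocol article*

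**What the plan says.** All references are to the Protocol article.

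- **Randomization.** Allocation is 1:1 by permuted blocks, and "patients will be stratified in a 1:1 fashion according to the enrolling hospital". The stated reason is to limit confounding by local differences in treatment, with postoperative care as the example. Hospital is the only stratum. Design and setting names two centers, one in Taiwan and one in China.
- **Secondary endpoints.** The continuous outcomes include node counts along each recurrent laryngeal nerve, operating times, blood loss, ventilation time, and "length of ICU stay (expressed in hours), length of hospital stay (expressed in days").
- **Statistical analysis, continuous outcomes.** After a split into normally distributed and skewed variables: "Comparisons will be performed using Student’s *t* test and the nonparametric Mann–Whitney *U* test, respectively". No stratum or covariate is named.
- **Statistical analysis, categorical outcomes.** "Categorical secondary outcomes will be expressed as frequencies and compared with the Fisher’s exact test". A Cochran–Mantel–Haenszel (CMH) test is then added to "examine the differences in categorical outcomes between the two treatment groups after adjusting for study center and use of nCRT".
- **Statistical analysis, primary outcome.** The test named for it, a one-sided two-sample proportion test, is also unadjusted.
- **Analysis plan.** The same section says that a formal statistical analysis plan will be prepared before final data collection. It is not shown.

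**The concern.** The design and the analysis do not match for continuous outcomes. Stratifying by hospital balances the arms within each center, so a difference in level between the two hospitals largely cancels from the RE–VATE contrast. A two-sample t test does not know this. It leaves the between-hospital spread in its residual variance and so uses a standard error larger than the true sampling variability.

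The protocol's own example of local variation is postoperative care, which bears most directly on ventilation time, ICU stay and hospital stay. Node yield, recovery and length of stay are also named secondary objectives. The sample size rests on the binary primary outcome alone, so no power was planned for these comparisons. What is at stake is a real difference missed because the test is less sensitive than the design allows. A false positive is not the risk here.

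**Working it through.** **Plan's own figure.** There is none on this point. The protocol gives no SD, target difference, power or center effect for any continuous outcome. Its 95 evaluable patients per arm (Sample size calculation) belong to the primary outcome and serve below only as the number analysed.

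**Inputs from the protocol.** Two centers; 1:1 allocation stratified by hospital only; significance at P < 0.05, read here as two-sided for secondary outcomes.

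**Assumptions.** *d* is the between-center difference in within-center SDs, shown over a range. *p* is the share of patients in one center. The effect is one that the center-adjusted test detects with 80% power.

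**Step 1. Variance seen by the t test.** Within an arm, the variance over both centers is σ²[1 + p(1−p)d²]. With equal centers, p(1−p) = 0.25.

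**Step 2. True variability.** Both arms have the same center mix, so the center term cancels and the difference in means has the within-center standard error. The t test uses r times that, where r = √[1 + p(1−p)d²].

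**Step 3. Power and type I error.** The standardized effect is 1.960 + 0.842 = 2.802. Hence power = P(Z > 1.960r − 2.802), and type I error = 2·P(Z > 1.960r).

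Example, d = 1.0 with equal centers: r = √1.25 = 1.118; 1.960 × 1.118 = 2.191; power = P(Z > −0.61) = 73%; type I error = 2·P(Z > 2.191) = 2.8%.

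| d | r, equal centers | power | type I error | r, 80/20 split | power | type I error |
|---|---|---|---|---|---|---|
| 0 | 1.000 | 80% | 5.0% | 1.000 | 80% | 5.0% |
| 0.5 | 1.031 | 78.3% | 4.3% | 1.020 | 78.9% | 4.6% |
| 0.75 | 1.068 | 76.1% | 3.6% | 1.044 | 77.5% | 4.1% |
| 1.0 | 1.118 | 72.9% | 2.8% | 1.077 | 75.5% | 3.5% |
| 1.25 | 1.179 | 68.8% | 2.1% | 1.118 | 72.9% | 2.8% |

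Equal centers maximize p(1−p), so the left block is the largest loss for each d. The 80/20 split is only an illustration, because the protocol gives no enrolment split.

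**Step 4. Check by simulation.** 4,000 runs per scenario; 95 per arm; two nearly equal centers (96 and 94 patients) balanced within center; nCRT in 50% and not stratified; true effect 0.4 within-center SD. The t test was compared with a linear model containing treatment, center and nCRT. Monte Carlo error on power is about √(0.7 × 0.3/4000) = 0.7 points.

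| Scenario | t-test SE (mean) | true SD of difference | t-test type I error | power, t test | power, adjusted |
|---|---|---|---|---|---|
| no center or nCRT effect | 0.145 | 0.144 | 5.1% | 77.7% | 77.7% |
| center effect 0.5 SD | 0.149 | 0.143 | 4.2% | 75.0% | 76.5% |
| center effect 1 SD | 0.162 | 0.145 | 3.0% | 70.0% | 77.9% |
| nCRT effect 1 SD, no center effect | 0.162 | 0.161 | 4.6% | 70.0% | 78.6% |

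The two center rows agree with the formula: 0.162/0.145 = 1.12 at 1 SD, with losses of 1.5 and 7.9 points. The nCRT row behaves differently. The standard error matches the true variability and type I error is near 5%, so the unadjusted test is valid. Adjustment still gains power, because it removes variance that chance imbalance in nCRT really does add.

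**The case against.** **It belongs to the analysis plan.** Adjustment of secondary outcomes is often left to that document, which is pending, and nothing here forbids adding it. This lowers the weight of the point. It does not remove it: the article names the tests for continuous outcomes and extends adjustment to categorical outcomes only, so this is a stated choice rather than a silence.

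**The contrast between outcome types is not clean.** A reader might infer that the plan adjusts its categorical outcomes and leaves only the continuous ones unadjusted. The text does not support that. Fisher's exact test and the primary proportion test are unadjusted too. What holds is narrower: categorical outcomes have an adjusted test beside the unadjusted one, and continuous outcomes have none.

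**The loss is not certain.** A reader might also infer that standard errors are too wide for both factors and that power is necessarily lost. The overstatement arises only for center, and only if center is prognostic. The protocol offers postoperative care as its one example. It does not say that node counts, operating time or blood loss differ between hospitals, and it works against such differences through a common lymphadenectomy standard, common nodal station definitions, a surgeon experience threshold and video review. A difference of 0.75 to 1.0 SD is therefore an assumption.

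**The figures are for the t test.** If stay, ventilation time or blood loss is skewed, the protocol assigns Mann–Whitney U. The same reasoning applies to a rank test that ignores the stratum, but its loss was not calculated.

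All four objections narrow the claim. None removes the mismatch between the stratified design and the tests named for continuous outcomes.

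**Conclusion.** The point holds as a minor, low-cost improvement. For continuous secondary outcomes the protocol names no analysis that uses the factor on which it stratifies. If center is prognostic, the t test is conservative. With two equal centers and 80% adjusted power, about 2 points of power are lost at a between-center difference of 0.5 SD and about 7 at 1.0 SD. At an 80/20 split the losses are about 1 and 4.5 points, and with no center effect there is none. For nCRT the unadjusted analysis is valid and adjustment only adds precision.

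These sizes rest on an assumed center effect, an assumed enrolment split and the t test. Type I error stays at or below 5%, and the sample size and primary conclusion are unaffected. The documents do not support reading this as a demonstrated loss of power or as an invalid analysis.

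**What to change.** State in the Statistical analysis section, or in the pending analysis plan before treatment allocation is revealed, that continuous secondary outcomes will be analysed with:

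- a linear model containing treatment, center and nCRT in place of Student's t, on the log scale where the outcome is skewed and positive; or
- the van Elteren test (Wilcoxon stratified by center and nCRT) in place of Mann–Whitney U. This suits outcomes that can be zero, such as node counts.

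Name in advance which method applies to which outcome, and keep the unadjusted tests as supportive. A log-scale model reports a ratio of geometric means, so the effect measure should be stated with it.

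The cost is a sentence or two. The protocol already plans to use center and nCRT in the CMH test, so no further data or patients are needed, and both methods can be run in the SAS package that it names.
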